# Repetitive application of remote ischemic conditioning (RIC) in patients with peripheral arterial occlusive disease (PAOD) as a non-invasive treatment option: study protocol for a randomised controlled clinical trial

**DOI:** 10.1186/s12872-022-02795-3

**Published:** 2022-08-04

**Keywords:** Remote ischemic conditioning (RIC), Repeated RIC, Chronic RIC, Peripheral arterial occlusive disease (PAOD), Randomized controlled trial

## Abstract

**Background:**

The best medical treatment (BMT) for most patients with early stage of peripheral arterial occlusive disease (PAOD) is often limited to gait training and pharmacological therapy besides endovascular surgery. The application of remote ischemic conditioning (RIC) has been described as a promising experimental strategy for the improvement of therapeutic outcome in cardiovascular disease but has not proven beneficial effects in clinical practice and treatment of PAOD yet.

**Methods:**

Here we describe a prospective, randomized trial for the evaluation of possible effects of repeated application of RIC in patients with PAOD. This monocentric study will enrol 200 participants distributed to an intervention group receiving RIC + BMT and a control group only receiving BMT for four weeks. Patients are at least 18 years of age and have diagnosed PAOD Fontaine stage II b. Pain-free and total walking distance will be measured via treadmill test (primary endpoints). In addition, ankle-brachial index (ABI) and quality of life (QoL) will be assessed using the SF-36 and VascuQoL-6 questionnaire. Moreover, evaluation of markers for atherosclerosis, angiogenic profiling and mononuclear cell characterization will be performed using biochemical assays, proteome profiling arrays and flow cytometry (secondary endpoints).

**Discussion:**

Our prospective, randomized monocentric trial is the first of its kind to analyse the effects of chronic and repetitive treatment with RIC in patients with PAOD and might provide important novel information on the molecular mechanisms associated with RIC in PAOD patients.

*Trial registration:* Prospectively registered in the German Clinical Trials Register (Deutsche Register Klinischer Studien) Registration number: DRKS00025735; Date of registration: 01.07.2021.

## Background

Due to demographic and lifestyle changes in modern society Peripheral Arterial Occlusive Disease (PAOD) has become one of the most common diseases worldwide [1]. For most patients suffering from PAOD with moderate to severe symptoms only pharmacological therapy and gait training remain as a therapeutic option until the course of the disease leads to unavoidable endovascular and open vascular surgical procedures. Accordingly, multiple advanced therapeutic approaches have been invastigated in order to overcome the actual limitations in the treatment of PAOD.

The concept of remote ischemic conditioning (RIC) has been evaluated as a promising strategy for patients with cardiovascular disease and may offer new treatment and rehabilitation options for patients with PAOD. RIC as a therapeutic strategy includes repeated, non-lethal episodes of ischemia to an organ or limb exerting protection and potentially faster regeneration from ischemia–reperfusion (I/R) injury [2]. This effective, simple and low-risk procedure can be easily induced by transient occlusion of blood flow with a blood pressure cuff located on the upper arm [3, 4].

However, only small and heterogenous studies have evaluated the potential effects of RIC on patients with PAOD. Unfortunately, most of these studies employed a single and limited application of RIC [5, 6]. Recent studies suggested that daily repeated RIC (chronic RIC; cRIC) might be more effective for cardiovascular protection than a single RIPC application (Chong et al. 2019). Therefore, the here described study aimed to investigate for the first time the long-term application of RIC on a homogeneous cohort of patients with PAOD Fontaine stage II b and investigate underlying molecular mechanisms.

## Methods

### Hypothesis

We hypothesize that long-term, repetitive application of RIC in combination with best medical treatment (BMT) including systematic gait training and pharmacological standard therapy will lead to longer painless and total walking distance, better quality of life (QoL) and an enhanced ankle-brachial index (ABI), when compared to standard BMT therapy in the control group.

### Study registration and ethical approval

The here described study protocol has been approved by the institutional ethic committee of the University Hospital Schleswig–Holstein (UKSH) (protocol number: D563/20) and has been registered in the *German Clinical Trials Register* (Deutsche Register Klinischer Studien = DRKS; Registration number: DRKS00025735). The study protocol follows the Standard Protocol Items: Recommendations for Interventional Trials (SPIRIT) guidelines. All patients will be assigned randomly 1:1 into two different groups through random permuted blocks. Enrolment of patients will be supported by two study nurses, guided by the cardiovascular outpatient department of the University Hospital Schleswig–Holstein and documented by a study diary. Written declaration of consent will be available for the enrolled patients.

### Study design

This study is a randomized, controlled monocentric trial, as presented in Fig. 1. For a schematic representation of the study, please refer to Fig. 2.

**Fig. 1 Fig1:**
[figure not shown]
SPIRIT Flow diagram for inclusion and treatment. ABI = ankle-brachial index; BMT = best medical treatment; PAOD = peripheral arterial occlusive disease; remote ischemic conditioning (RIC), QoL = quality of life

**Fig. 2 Fig2:**
[figure not shown]
Schematic depiction of the study and long-term follow-up

### Patients

A total of 200 patients (minimal number to treat 120) with diagnosed PAOD Fontaine stage II b and aged over 18 years will be randomised if written consent is given.

### Primary endpoints

Primary endpoint of the study is the improvement of the pain-free and total walking distance after RIC + BMT compared to BMT in the control group, respectively. The determination of the pain-free and total walking distance and classification according to the Fontaine classification stage I-IV will be assessed by a standardized treadmill-test at 3.2 km/h (2 miles/h) and an incline of 12% on the treadmill. Moreover, improvement of the ankle-brachial index (ABI) and the Quality of Life (QoL) will be determined by the SF-36 and VascuQoL-6-test (Fig. 1).

### Secondary endpoints

Secondary endpoints will be assessed to determine the correlation between the development of collateral blood vessels and clinical symptoms and to identify any other beneficial effects of RIC in the PAOD clinical scenario. The following secondary objectives will be assessed:Influence of RIC on renal function, serum creatinine (improvement of pre-existing renal insufficiency)Determination of the effects of RIC on limb perfusion using thermal imaging cameraComparison of laboratory chemical markers for atherosclerosis HS-CRP, cholesterol, IL-6, Il-1, fibrinogen, homocysteine, lipoprotein-(a)Molecular biology and protein biochemistry analyses on the influence of RIC on the protein expression profile of proangiogenic and ischemia-protective factorsNumber of circulating mononuclear cells (CD14, CD26, CCR2, CX3CR1, CD105, TIE2)

### Eligibility criteria

Patients meeting the following criteria will be *included* in the study protocol:Occurrence of PAOD II b for at least four weeksNo surgical or interventional treatment within the last to weeksWritten informed consent

While patients with the following conditions will be *excluded* from the study protocol:Age < 18 years > 75 yearsCurrent participation in another clinical intervention studyParticipation in another clinical intervention study within the last 30 daysCognitive/language barriers, comprehension problems during the informed consent processSevere renal and hepatic insufficiencySevere COPD (FeV1 ≤ 50%)Existing drug and alcohol abuseNeurological diseases (Parkinson's disease, multiple sclerosis, epilepsy, Alzheimer's disease)Acute infectionsPronounced PAOD of the upper extremitiesPolyneuropathy of the upper extremitiesArterio-venous fistula (shunt) or lymphedema of the upper extremitiesMyocardial infarction < 2 monthsStroke < 2 monthsMalignancyPregnancyLack of compliance, > 3 missed RIC applications

### Randomization

Central randomization will be performed by block randomization with use of an automated web-based randomization tool.

### Study intervention

Repetitive, non-injurious ischemia will be induced by inflation and deflation of a blood pressure cuff at the upper limbs with a defined pressure of 200 mmHg. The mechanism of tissue/organ protection by RIC is mainly based on activation of neuronal efferences, systemic anti-inflammatory responses and the release of humoral factors via the bloodstream [3, 4]. Additionally, RIC might have a beneficial effect on chronic remodelling processes and angiogenesis which is highly relevant for treatment of PAOD [2, 3, 5, 6].

Application of RIC has been classified as a non-painful intervention, but with slightly unpleasant symptoms (numbness, tingling paraesthesia, which are completely reversible after a short time). Conceivable side effects of RIC such as thrombosis, arterial plaque rupture, nerve and vascular injury did not occur in any patient in the large phase III studies conducting a RIC protocol [8, 9]. Here we describe a repetitive, chronic RIC application for 3 × 5 cycles (each with 5 min ischemia and 5 min reperfusion) on day 1, 3, 5, 8, 10, 12, 15, 17, 19, 21, 24, 26. The treatment and follow-up will be supported by two study nurses and a study diary to increase the patient compliance.

### Adverse events and stop criteria

Adverse events (AE) are defined as any undesirable event occurring to the study participants during the clinical trial, whether or not considered related to the investigational treatment. All AEs and serious AEs reported spontaneously by the subject or observed by the investigator or his staff will be recorded using an AE form during admission and throughout 24 months of follow-up.

If stop criteria occur, study participants will immediately stop RIC treatment and the cardiovascular surgery outpatient department clinic or study investigators will be informed. The Ethic Committee will be notified immediately of any incident.

The following stop criteria are designated for RIC:persistent swelling and redness of the armpersistent paraesthesia, despite termination of RICpersistent pain, despite termination of RICformation of large hematomas in the skin after RIC

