### Follow-up

The trial will be supported by two study nurses respectively research assistants during the study course. Any complications will be recorded and additionally the patients will fulfil a mandatory study diary to increase compliance. At day 28 all patients will undergo a second treadmill test, ABI and final interviews for assessment of QoL (Fig. 2). Blood samples will be collected for further analysis of secondary endpoints. A further six months and twelve months follow-up will be provided by investigation of pain-free walking distance, ABI and again QoL to observe long-term effects of RIC in patients with PAOD.

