## Discussion

Optimized treatment of PAOD remains a major and interdisciplinary challenge in current medicine [10]. Recent clinical studies have provided evidence that RIC could be a beneficial treatment option for cardiovascular disease in general but have also shown that large heterogenous trials and patient cohorts might not be the tools of first choice [5, 6, 8, 9]. Therefore, we here describe a trial design that will clarify the potential influence of RIC on relevant outcome parameters and QoL in patients with PAOD stage II Fontaine. Until today, only a few clinical studies have investigated the potential influence of RIC on PAOD with a limited number of patients and single respectively limited treatments [5, 6]. In contrast we hypothesised that chronic, repeated application of RIC might be necessary to generate PAOD-related therapeutic effects such as angiogenesis and collateral growth based on the knowledge that cardiovascular remodelling is often based on repeated stimuli [11, 12]. We have therefore conducted a study design that includes 3 × 5 RIC cycles per treatment day over a time period of 28 days. To the best of our knowledge this will be the first study to investigate this kind of repetitive RIC treatment in patients with PAOD.

A particular strength of this study might be the close monitoring of the patients during the trial which is represented by the employment of study nurses/research assistants providing weekly telephone/video feedbacks and a study diary. These aspects could be key factors to increase compliance and avoid the relatively high dropout rates described in similar trials [13].

Further, the here described study design not merely includes the clinical evaluation of the study patients but also conducts an experimental set-up taking into account the analysis of pro-angiogenetic protein levels and cellular transformation of mononuclear cell lines potentially influenced by RIC treatments [14, 15]. Accordingly, this study will provide insights not only in clinical outcome but also in molecular mechanisms associated with the effects of RIC treatment [16]. This monocentric trial design might represent a blueprint to enable further potential multicentric studies in patients with PAOD undergoing repetitive RIC application.

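### Passive adverse-event capture with a BMT-only control and no stated sham leaves the comparison of non-serious events open to ascertainment bias, and no scheduled check for the named harms is stated

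*Protocol article*

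**What the plan says.** All statements are from the protocol article.

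- **Capture rule** (Adverse events and stop criteria). The definition is broad: any undesirable event in a participant, related to treatment or not. The method is: "All AEs and serious AEs reported spontaneously by the subject or observed by the investigator or his staff will be recorded", on an AE form. The period is "during admission and throughout 24 months of follow-up".
- **Comparator** (Abstract, Methods). The trial has "a control group only receiving BMT for four weeks". Study design adds only: "This study is a randomized, controlled monocentric trial". Neither a sham cuff nor blinding is mentioned.
- **Exposure and named harms** (Study intervention). RIC is given on 12 listed days. Numbness and tingling are expected. The section also refers to "Conceivable side effects of RIC such as thrombosis, arterial plaque rupture, nerve and vascular injury", and says that none was seen in the large phase III trials it cites.
- **Stop criteria** (Adverse events and stop criteria). Four arm signs are listed, for RIC only: swelling with redness, paraesthesia, pain and large haematoma. If one occurs, RIC stops and the clinic or the investigators are told. The ethics committee is notified of any incident.
- **Contacts** (Follow-up and Discussion). Day 28 has a treadmill test, ABI, QoL interviews and blood samples for all patients. After that: "A further six months and twelve months follow-up will be provided by investigation of pain-free walking distance, ABI and again QoL". Follow-up also says that complications are recorded and that patients keep a mandatory diary, whose stated aim is compliance. The Discussion describes study staff "providing weekly telephone/video feedbacks and a study diary", again with compliance as the aim.

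**The concern.** Under spontaneous reporting, an event enters the data only if the patient notices it, thinks it worth mentioning and has someone to tell, or if staff happen to see it. In this design the first two steps can differ by arm. Patients can tell whether they are being cuffed. The RIC arm has known arm sensations and a list of arm signs to watch for, and the control arm has neither. A difference in recorded non-serious events could then reflect reporting as well as treatment.

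There is a second consequence. The article names thrombosis, plaque rupture, nerve injury and vascular injury as conceivable, but no listed visit content asks about or examines for them. If none is recorded, the reader cannot tell how far that reflects absence and how far it reflects the absence of a prompt.

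What is at stake is how the tolerability data can be read. The Discussion presents this as the first study of this repetitive regimen in PAOD and as a possible model for multicentre trials, so others may reuse those data.

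**Working it through.** The article gives no AE rate, capture probability or planned AE test, so there is no figure to reproduce. The check has two parts.

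**1. What each relevant statement does for capture**

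| Text | Does it elicit events? | Alike in both arms? |
|---|---|---|
| AE rule and form | No: volunteered or observed | Yes, the rule covers all participants |
| Complications recorded (Follow-up) | Says to record, not how events are found | Not restricted to one arm |
| Stop criteria | Prompt attention to four arm signs | No, RIC only |
| Diary | Not described as asking about AEs | Not restricted to one arm |
| Weekly calls | Not described as asking about AEs | Not restricted to one arm |
| Day 28, 6 and 12 months | Walking, ABI and QoL, with blood at day 28; no AE question or arm examination listed | Day 28 covers all patients; later visits not restricted to one arm |

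The only prompt to look for arm events applies to one arm. The contacts that could carry a common prompt exist but are not given that task. AE recording runs to 24 months, while the last visit stated in the text is at 12 months. Between those times the passive rule is the only source stated.

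**2. Illustration of unequal capture (all rates assumed)**

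Let the true event risk p be the same in both arms, with capture probabilities c_RIC and c_BMT.

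- Recorded risk = p × c.
- Recorded risk ratio = (p × c_RIC) / (p × c_BMT) = c_RIC / c_BMT. The true risk cancels.
- 0.60 / 0.50 = 1.2 and 0.80 / 0.50 = 1.6. With the capture figures swapped between arms, 0.50 / 0.60 = 0.83 and 0.50 / 0.80 = 0.63.

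In counts, 200 patients at 1:1 is 100 per arm. At p = 20% there are 20 true events in each arm. Capture of 50% records 10, 60% records 12 and 80% records 16.

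If the recorded risks were compared at two-sided 0.05, the chance of a nominally significant RIC excess is Φ(z), where

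z = [d − 1.96 × √(2 p̄(1 − p̄)/n)] / √{[p1(1 − p1) + p2(1 − p2)]/n},

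p1 and p2 are the recorded risks, d is their difference and p̄ is their mean. For 10% vs 16% and n = 100: (0.06 − 1.96 × 0.0476) / 0.0474 = −0.70, so the chance is about 24%.

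| True risk, both arms | Recorded, capture 50% vs 60% | Chance | Recorded, capture 50% vs 80% | Chance |
|---|---|---|---|---|
| 10% | 5% vs 6% | 5% | 5% vs 8% | 13% |
| 20% | 10% vs 12% | 7% | 10% vs 16% | 24% |
| 40% | 20% vs 24% | 10% | 20% vs 32% | 49% |

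The formula counts only the tail that favours a RIC excess, so the no-bias benchmark is 2.5%.

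**The case against.** **The rule is even-handed and not the only safeguard.** One definition, one rule and one form apply to every participant. Complications are to be recorded, there is a diary, and all patients are seen at day 28. This stands in part. A reader might infer that the arms cannot be compared for harm at all. The documents do not support that: serious events depend much less on prompting, and the size and direction of any bias are unknown. But a common form does not equalise what reaches it, and no statement other than the AE rule says how events are found.

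**Arm signs are watched for.** A reader might infer that arm injury is simply not looked for. That is also too strong, because four arm signs are named and trigger action. What is missing is an active, scheduled check used alike in both arms. The stop criteria concern stopping RIC, so they give no such check in controls or after treatment.

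**Extra contact in the RIC arm is assumed.** This stands. The article does not say that sessions take place in front of staff, so 12 treatment days are not shown to be 12 extra contacts. That the trial is open-label is likewise inferred from the BMT-only control.

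**No safety endpoint or between-arm AE test is planned.** This stands. A reader might take safety to be a main output, but the hypothesis and endpoints concern walking distance, ABI, QoL, renal function, perfusion and biomarkers. The point is therefore about how AEs are described, and the chances in the table apply to a test that the article does not announce.

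**The article is condensed.** Diary items, call scripts and AE forms may sit in the full protocol, and their absence here is no finding. The passive rule, however, is written out and can be judged as it stands.

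**Conclusion.** The concern holds in a limited form. The article fixes a passive capture rule in a trial with a BMT-only control, no stated sham and arm-sign stop criteria for RIC alone. Any between-arm description of non-serious AEs is open to ascertainment bias, and serious AEs less so. No active, scheduled check is stated for the harms that the article itself names.

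The size cannot be derived from the documents. The spurious ratios of 1.2 and 1.6 are the ratios of assumed capture probabilities, and if control events were the better captured the ratio would fall below 1. They show that a moderate difference in capture can look like a treatment effect; they do not show that it will. The conclusion assumes that patients know their allocation, which follows from the design as described but is not stated.

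**What to change.** In Adverse events and stop criteria, keep spontaneous reporting and staff observation, and add:

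1. One short, fixed AE question list, worded identically for both arms. It covers arm symptoms (pain, swelling, paraesthesia, haematoma) and limb, cardiac and cerebral events.
2. Its use as a diary item, at the weekly calls, and at the day-28, 6- and 12-month visits, with a statement that calls follow the same schedule in both arms.
3. Separate reporting of solicited and volunteered events, by arm.

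In the same edit, reconcile the 24-month AE period with the 12-month last visit in Follow-up. The stop criteria need no change for this.

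**Cost.** One added form at contacts the trial already describes, with no extra visit. If the weekly calls currently go to one arm only, which the text does not say, extending them would take staff time. More minor events will be recorded. Prompting also does not fully remove reporting bias, because patients who know they were cuffed may still endorse arm symptoms more readily.

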### Statistical analysis

All calculations for the planned number of cases were performed using the G*power 3.1 software (http://www.gpower.hhu.de) and StatMate (Graphpad, San Diego, USA). Data will be analysed with the latest version of the Graphpad prism software (Graphpad Software, San Diego, USA). A drop-out rate of 20% was calculated for the trial design and a minimum of 120 patients should be included. D'Agostino‐Pearson or Kolmogorov‐Smirnov test will be used for normality testing. Paired respectively unpaired student's t test will be used for metric and Wilcoxon-Mann–Whitney-Test will be used for non-metric data with regard to the primary and secondary endpoints.

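### The exclusion for more than three missed RIC applications does not separate safety stops from non-compliance, so RIC patients who cannot tolerate the cuff may be lost from the efficacy comparison

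*Protocol article*

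**What the plan says.** Four sections of the protocol article bear on this point.

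- **Study intervention.** The treatment is described as "repetitive, chronic RIC application for 3 × 5 cycles (each with 5 min ischemia and 5 min reperfusion", given "on day 1, 3, 5, 8, 10, 12, 15, 17, 19, 21, 24, 26". The Discussion makes clear that the 3 × 5 cycles are the dose for each treatment day.
- **Adverse events and stop criteria.** "If stop criteria occur, study participants will immediately stop RIC treatment". The triggers are persistent swelling and redness of the arm, persistent paraesthesia, persistent pain, and large skin hematomas. No restart is described. An adverse event is defined as "any undesirable event occurring to the study participants during the clinical trial", related to treatment or not, and all such events "will be recorded using an AE form during admission and throughout 24 months of follow-up".
- **Eligibility criteria.** The last item in the exclusion list is poor compliance, quantified as more than three missed RIC applications. It does not distinguish reasons for missing an application.
- **Follow-up.** "Any complications will be recorded", and "At day 28 all patients will undergo a second treadmill test, ABI and final interviews for assessment of QoL". Further assessments follow at six and twelve months.

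The Statistical analysis section allows for loss in numbers ("A drop-out rate of 20% was calculated for the trial design and a minimum of 120 patients should be included") but does not say how patients who stop RIC are handled.

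**The concern.** A missed-application count cannot be known at enrolment, so this exclusion can act only after randomisation. Controls have no applications to miss, so it can act only in the RIC arm. A patient whose cuff treatment is stopped for persistent pain or paraesthesia then collects unapplied sessions, which the exclusion, as worded, counts like sessions skipped by choice.

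The efficacy comparison is what is at stake. If such patients are taken out, the RIC arm that is compared on walking distance and quality of life consists more of people who tolerated the cuff. Control patients with the same prognosis stay in, because nothing in their arm can identify them. Quality of life is the most exposed outcome, since lasting arm pain or paraesthesia is both a reason to stop and a plausible cause of a worse score. Whether a patient with a given reaction is kept would also depend on the day on which it occurred.

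**Working it through.** The article gives no figure for this point, so there is none to reproduce. The check counts sessions.

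**Inputs**
- 12 treatment days: 1, 3, 5, 8, 10, 12, 15, 17, 19, 21, 24, 26 (Study intervention).
- Exclusion threshold: more than 3 missed, that is 4 or more (Eligibility criteria).
- Immediate stop, no restart described (Adverse events and stop criteria).
- Assumption: no session was missed earlier for another reason.

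**Step 1: one application per treatment day.** If RIC stops after session k, the number not given is m = 12 − k. The threshold is crossed when 12 − k > 3, that is k ≤ 8.

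| Last session given (k) | Day | Not given (12 − k) | More than 3? |
|---|---|---|---|
| 1 | 1 | 11 | yes |
| 2 | 3 | 10 | yes |
| 3 | 5 | 9 | yes |
| 4 | 8 | 8 | yes |
| 5 | 10 | 7 | yes |
| 6 | 12 | 6 | yes |
| 7 | 15 | 5 | yes |
| 8 | 17 | 4 | yes |
| 9 | 19 | 3 | no |
| 10 | 21 | 2 | no |
| 11 | 24 | 1 | no |
| 12 | 26 | 0 | no |

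The boundary lies between day 17 and day 19: 8 of the 12 possible stopping points cross the threshold.

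**Step 2: sensitivity to the meaning of an application.** The article does not say whether an application is a treatment day or each of the three five-cycle sets on that day. Counting sets, the number not given is 3 × (12 − k), and 3 × (12 − k) > 3 holds for k ≤ 10. After day 21 the count is 3 × 2 = 6, which crosses; after day 24 it is 3 × 1 = 3, which does not. That makes 10 of 12 stopping points.

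**Step 3: effect of an earlier miss.** With one session already missed on the day count, a stop after day 19 gives 3 + 1 = 4 and also crosses. The day-17 boundary is therefore the most lenient case.

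**Step 4: the rules side by side.** For a patient stopped after day 10, say, the stop rule withholds 7 sessions. The Follow-up section, which speaks of all patients, would bring this patient to the day-28 assessment. The exclusion list, read literally, would remove the same patient because 7 > 3. No sentence in the article says which applies.

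**The case against.** The strongest reply is that the sections can be reconciled. The criterion is labelled as a compliance failure, and a patient who stops because the protocol orders it is complying. The stop rule ends RIC treatment, not study participation, and the day-28 assessment is for all patients. This is a reasonable reading, and it is why exclusion cannot be called automatic. It is not the only reading, however: the threshold is a bare count without reference to reason, and the article does not say whether all patients includes those excluded under it. Staff could apply either reading case by case.

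A reader might also infer that harms of RIC would disappear from the results. The documents do not support that. All adverse events are to be recorded through 24 months, any complication is to be recorded, and nothing says that the events of excluded patients are discarded. The event that triggers a stop falls under that recording rule. What is exposed is the efficacy and quality-of-life comparison, not the adverse event record.

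A third reply is that analysis populations belong in the full protocol or analysis plan, which is not shown. That is right, and the absence of a named population is not the complaint. The complaint is that the article itself states a numeric, post-randomisation exclusion that acts in one arm only.

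Finally, safety stops are only part of the patients whom this exclusion can reach; someone who skips sessions because of mild discomfort is caught too. This stands, and an exemption limited to safety stops would leave that selection in place. The fix below therefore changes the status of the threshold itself.

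**Conclusion.** The point holds as a gap between two stated rules. The exclusion does not distinguish applications withheld for safety from applications missed through non-compliance. On a literal reading, a safety stop after any session up to day 17 (8 of 12 stopping points), or up to day 21 if each daily set counts (10 of 12), puts a RIC patient over the threshold. The loss would be confined to the RIC arm and would probably favour RIC; the direction is a judgement, not a calculation.

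The size of the bias cannot be given, because the article states no expected rate of safety stops. It is tempting to read 8/12 and 10/12 as 67% and 83% of stopped patients being lost. That would require reactions to be spread evenly over the sessions, for which the documents give no basis. The fractions describe the schedule, not patients. The number affected may be small. The 20% drop-out allowance does not answer the point, since it covers reduced numbers and not selective loss from one arm.

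The conclusion rests on three assumptions: RIC is not restarted after a stop, no earlier session was missed, and the exclusion is applied as worded.

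**What to change.** Leave the stop criteria as they are and add a few sentences to Eligibility criteria and to Adverse events and stop criteria:

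1. Applications withheld because a stop criterion was met are not missed applications and are not non-compliance.
2. More than three missed applications is recorded as an adherence deviation, usable to define a per-protocol sensitivity analysis, and is removed from the exclusions. State whether an application is a treatment day or a five-cycle set.
3. Patients who stop RIC for safety, or who exceed the threshold, stay in their randomised arm, attend the day-28, six-month and twelve-month assessments, and are included in the primary analysis.
4. Discontinuations of RIC for a stop criterion are reported separately from sessions missed for other reasons, as a tolerability result.

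The visits and the adverse event form already exist, so the cost is drafting. The statistical price is slight dilution of the observed effect, because some patients counted in the RIC arm will have received only part of the treatment.
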